#### Concealment mechanism {16b}

The concealment mechanism is provided by REDCap^®^, which allows the user to preform randomization without the possibility of knowing the outcome beforehand. While blinding clinicians to treatment allocation is desirable, it is not deemed feasible for this study. We minimize bias through allocation concealment.

#### Implementation {16c}

The allocation sequence will be generated by a person not involved with enrollment or future analysis. Participants will be screened and randomized on admission to the operating room by a site investigator or member of research support staff.

### Assignment of interventions: blinding

#### Who will be blinded {17a}

Physicians and anesthetic nurses in the theater room cannot be blinded for the randomized arm. Physicians, nurses in PACU and in the surgical ward, and patients will be kept blinded for the randomized arm. Data analysts will be blinded for the randomized arm. Outcomes are mainly objective abstracted from electronic data to reduce bias.

#### Procedure for unblinding if needed {17b}

The design is an open label with only the statisticians/data analysts being blinded so unblinding will not occur.

### Data collection and management

#### Plans for assessment and collection of outcomes {18a}

All study data will be collected by an investigator of the research staff at each site using an eCRF and stored in a password-protected, traceable database (REDCap^®^) managed by the promotor (Clermont-Ferrand University). All parameters are defined in a data dictionary detailing the way in which data should be collected. The study promotor will ensure site visits for data monitoring, timely resolution of queries, and correction of errata during quality control checks.

#### Plans to promote participant retention and complete follow-up {18b}

The intervention is to be administered soon after operating theater admission and will last a short duration of time, likely while participants are unconscious. Patients will be approached once conscious and practical to do so, to inform them of study progress and follow-up required by a phone call at day 28. Obtaining data from medical records will ensure complete follow-up until patient discharge.

#### Data management {19}

Study data will be collected and managed using REDCap^®^ electronic data capture tool hosted and managed by the promotor (Clermont-Ferrand University) [24]. REDCap^®^ allows for a secure support data capture for research studies, providing audit trails for tracking data manipulation and export procedures, automated export procedures for common statistical software and procedures for data integration and interoperability with external sources.

#### Confidentiality {27}

According to the French and Canadian laws, each personnel who have a direct access to data will have to take all necessary precautions to ensure confidentiality of information related to experimental drugs, trials, and participants especially about their identity. Personnel as an investigator are bound by professional secrecy. The anonymity of each participant is ensured by a code number and initial of participants on the research documents. Identifying documents such as consent forms will be kept in locked rooms that may only be accessed by authorized personnel.

#### Plans for collection, laboratory evaluation, and storage of biological specimens for genetic or molecular analysis in this trial/future use {33}

Please see item 26b, this trial does not involve collecting biological specimens.

## Statistical methods

### Statistical methods for primary and secondary outcomes {20a}

The main analysis will take the form of an intent-to-treat procedure using the Stata^®^ (version 13, StataCorp, College Station) and R (http://cran.r-project.org/) software; all of the statistical tests will be carried out with an α value of 5%. The continuous variables will be presented as mean and standard deviation, provided that distribution is normal (Shapiro-Wilk test, if required). In the event of an anomaly, they will be presented as median, quartiles, and ranges. Qualitative variables will be expressed in numbers and related percentages. Where feasible, graphs will accompany these analyses. Intergroup comparisons will be routinely carried out (1) without adjustment (2) by adjusting factors, the distribution of which might not be balanced between the groups, despite randomization.

The patients will be described and compared between the groups at baseline, according to the following variables: compliance with eligibility criteria, epidemiological characteristics, clinical characteristics, and possible treatments. The initial comparability of both arms will be assessed on the basis of the principal characteristics of participants and potential factors linked to the primary endpoint. Any difference between the two groups in terms of one of these characteristics will be determined based on clinical as opposed to purely statistical considerations. Protocol deviations, patients distributed according to these deviations, and reasons for withdrawal will also be described. The number of patients enrolled and the enrolment graph will be presented per group.

Since a 50% reduction in the incidence of immediate postoperative pain in PACU patients receiving ANI-directed intraoperative analgesia ranging from 50 to 80 must be highlighted, the primary endpoint (percentage of patients with NRS > 3) will be compared using the *x*^2^ paired test or Fisher’s exact test, if applicable.

Secondly, this analysis can be completed in a multivariate situation using a generalized, linear mixed model approach to logistics, considering inter- and intra-site variability. The covariables will be considered in terms of clinical relevance (other treatments, continuous use of vasopressors, type of surgery) and the results of previous univariate analyses. The results will be expressed in terms of related odds ratios and 95% confidence intervals.

For the other qualitative parameters (percentage of patients with a NRS > 3 on the first day following surgery, postoperative complications on the first and seventh days after surgery, and patient destination following surgery (surgery unit, continuous care, intensive care), analyses relating to the secondary objectives will focus on the same approach as that previously recommended for the primary endpoint.

The quantitative secondary endpoints (maximum pain score on the first day following surgery, PACU dose levels of morphine, total dose of morphine on the first day following surgery, duration of PACU (time taken to obtain an Aldrete score ≥ 9), duration of hospital stay) will be compared between the groups using Student’s *t* test or Mann-Whitney’s non-parametric test if the *t* test conditions are not respected (normality study, homoscedasticity studied using the Fisher-Snedecor test). The results will be expressed in terms of effect size and 95% confidence interval. These analyses can be completed a second time in a multivariate situation using linear regression models. The covariables will be considered in terms of clinical relevance and the results of previous univariate analyses. The results will be expressed in terms of related regression coefficients and 95% confidence intervals.

Survival on day 28 post-surgery will be estimated according to the Kaplan-Meier curve and compared between the randomization groups using the log-rank test in a univariate situation and Cox’s model in multivariate analysis. The results will be expressed in terms of the immediate relative risk ratio and 95% confidence intervals.

Part of the analyses concerning the secondary endpoints will be exploratory in nature and should lack statistical power. As discussed by Feise in 2002, adjustment of the *p* value will not be proposed routinely but on a case-by-case basis depending on clinical as opposed to purely statistical considerations [25].

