#### Sample size {14}

Given the fact that immediate postoperative pain can affect 30% of patients [1], a total of 161 patients per group (322 patients) will give 90% power using a bilateral test with a *p* value of 5% to detect a 50% reduction in the incidence of immediate postoperative pain (NRS ≤ 3) in patients guided by ANI. Given the specific features of this protocol (essentially the direct transfer from operating theater to continuous monitoring or ICU, use of continuous vasopressors), the final decision is to include a total of 380 patients (190 per group). An interim analysis will be scheduled halfway through the enrolment period (95 patients per group). The *p* value used to decide withdrawal from the trial on efficacy grounds is set at 0.003 (correction of the O’Brien-Fleming alpha-spending function).

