### Interim analyses {21b}

An interim analysis will be scheduled halfway through the enrollment period (95 patients per group).

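### The stated 5% level for all tests is not reduced for the final primary analysis after the 0.003 interim look, so the overall type I error is about 5.1% if the text is followed literally (minor).

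*Protocol article*

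**What the plan says.** Three sections of the protocol article bear on the level of the primary test.

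- **Sample size {14}** sizes the trial "using a bilateral test with a *p* value of 5"%: "a total of 161 patients per group (322 patients) will give 90% power". It then plans one look: "An interim analysis will be scheduled halfway through the enrolment period (95 patients per group"). The p value for stopping on efficacy grounds "is set at 0.003 (correction of the O’Brien-Fleming alpha-spending function").
- **Interim analyses {21b}** repeats the timing, "An interim analysis will be scheduled halfway through the enrollment period (95 patients per group"), and gives no limit for either look.
- **Statistical methods for primary and secondary outcomes {20a}** opens with the intention-to-treat main analysis and says that "all of the statistical tests will be carried out with an α value of 5"%.

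No section gives a lower level for the final primary test.

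**The concern.** An alpha-spending function divides one total error rate across the planned looks. What is spent at the interim is no longer available at the end, so the final nominal level must fall below the total. Here the interim limit comes from such a function, but the only level that the article states for the main analysis is the undivided 5%. An analyst who follows {20a} as written would spend 0.003 at the interim and then test again at 0.05. The total would exceed the 5% that the function is meant to protect.

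At stake is the decision rule for the confirmatory test of a superiority trial. If the final limit is not written down before the results are known, a p value just under 0.05 could be called positive or negative depending on which reading is chosen afterwards.

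**Working it through.** **Inputs** (Sample size {14} unless noted)

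- Two-sided level 0.05 (also {20a}).
- Interim nominal limit 0.003, O'Brien-Fleming-type spending.
- One look at 95 of 190 per group, so t = 95/190 = 0.5.
- Control rate 30% and a 50% relative reduction, so 30% against 15%; 161 per group for 90% power.

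**1. Reproduce the sample size.** With the pooled-variance formula and no continuity correction, the mean rate is 0.225 and

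n = [1.960 × √(2 × 0.225 × 0.775) + 1.2816 × √(0.30 × 0.70 + 0.15 × 0.85)]² / 0.15²

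= [1.960 × 0.5906 + 1.2816 × 0.5809]² / 0.0225 = 160.8, rounded up to **161**.

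The stated figure reproduces, and it uses the full 5% for a single test.

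**2. Reproduce the interim limit.** Lan-DeMets O'Brien-Fleming-type spending, with two one-sided boundaries of 0.025, gives

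2 × 2 × [1 − Φ(2.2414 / √0.5)] = 4 × [1 − Φ(3.170)] = **0.00305**.

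This rounds to the stated 0.003, so the interim limit is correct and corresponds to a total of 0.05. (The classical two-look O'Brien-Fleming boundary would be 0.0052 and 0.0480, so it is not the one in use.)

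**3. Overall error if the final test uses 0.05.** Under the null hypothesis the two test statistics are bivariate normal with correlation √0.5 = 0.707. The critical values are 2.968 (for 0.003) and 1.960 (for 0.05):

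1 − P(|Z₁| < 2.968 and |Z₂| < 1.960) = 0.05097, that is **0.0510**.

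A simulation of 20 million draws gives 0.0509. The excess is smaller than the 0.003 spent because most interim rejections would also be rejections at the end. The overlap is 0.003 + 0.05 − 0.05097 = 0.00203, about two thirds of 0.003.

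**4. Final level that restores 0.05.** Solving 1 − P(|Z₁| < 2.968 and |Z₂| < c) = 0.05 gives c = 1.968, a nominal p of **0.0490**.

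**5. Sensitivity to the information fraction.** Suppose the look is at 95 per group but only 161 per group are evaluable at the end. Then t = 95/161 = 0.59, the overall error is 0.0506, and the restoring final level is 0.0494.

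**6. Cost of the lower final level** (power of the final test alone, 30% against 15%)

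| Patients per group | Power at 0.05 | Power at 0.049 |
|---|---|---|
| 161 | 90.0% | 89.9% |
| 190 | 94.1% | 94.0% |

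Keeping 90% power at 0.049 needs 162 per group instead of 161.

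**The case against.** **The 5% may be the overall level.** The sentence in {20a} is a general statement on software and alpha, and it does not mention the interim look. A spending function is defined by a fixed total, and 0.003 is exactly what a total of 0.05 gives at half information. So 5% can coherently be read as the total, with about 0.049 implied at the end. This stands as a possible reading. It does not remove the point, because the text refers to all tests and says nowhere that 5% is a total.

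**A final boundary is often left to the analysis plan.** That is true, and neither the analysis plan nor the full protocol is at hand. Had the article been silent on the final level, there would be nothing to raise. It does state a level, and that level does not fit the function it names.

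**The excess is lost in the discreteness of the test.** This is fair. With binomial data, an uncorrected chi-square test, 190 per group and no interim look, the actual size at a nominal 0.05 runs from 0.0497 to 0.0523 for common event rates of 20% to 40% (0.0507 at 30%). With the look and a final level of 0.049 it is still 0.0506 at a 30% rate and 0.0523 at 40%. The correction aligns the written rule with the spending function, but it does not guarantee an exact 5% for these data.

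**A stronger reading to avoid.** A reader might infer from the reference to all tests that the interim look is also run at 5%, which would inflate the error far more. The documents do not support this: {14} sets 0.003 specifically for the interim decision, and a specific rule governs over a general sentence.

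**Conclusion.** The point holds as a minor one. Read literally, the plan has an overall two-sided type I error of about 5.1% for the primary endpoint (0.0510 at t = 0.5, 0.0506 at t = 0.59). Only a final p between about 0.049 and 0.050 would be classified differently.

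This assumes a single efficacy look at the stated 0.003, an information fraction of 0.5 to 0.59, the normal approximation to the chi-square test, and a final test at the full 5% as {20a} says. If the 5% was meant as the overall level, there is no excess and only the wording is at fault. The article does not settle which was meant.

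A reader might go further and infer that the trial lacks error control or that its sample size is inadequate. Neither follows: the excess is about 0.1 percentage point, the interim limit is correct, and the planned 190 per group keep power near 94%.

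**What to change.** In {20a}, replace the general sentence with a statement that 5% is the overall two-sided level for the primary endpoint, shared between the interim and final analyses. State in {20a} and {21b} that the interim efficacy limit is 0.003 and that the final primary test uses the remaining O'Brien-Fleming-type boundary: a nominal p of about 0.049 if the look takes place at 50% information, recomputed from the actual information fraction. The change should be fixed before results by arm are known.

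The cost is a few sentences and about 0.1 point of power at 161 per group. The planned total of 380 need not change.

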## Introduction

### Background and rationale {6a}

Severe postoperative pain remains a major problem that is seen in 20 to 40% of patients [1]. Numerous minor or average surgical procedures, some of which are performed by laparoscopy, trigger surprisingly high levels of postoperative pain [1]. To reduce the incidence of severe pain, patients who have undergone surgery, especially procedures deemed to be minor, should be monitored more precisely. Postoperative pain relief should conform to specific procedures and recommendations [2].

Narcosis (loss of consciousness), analgesia, and muscle relaxation are three major components of anesthesia. Unlike the other components, the assessment of analgesia (or “antinociception”), in current clinical practice, is based on clinical signs that are not very specific, such as movement, lacrimation, tachycardia, or hypertension. Optimized analgesia should individualize the nociception/antinociception balance and optimize the prevention of these reactions to surgical stimuli. In recent years, several monitors have been developed to measure the nociception/antinociception balance [3, 4].

Among them, the Analgesia/Nociception Index (ANI) has been developed to assess intraoperative analgesia using variations of the relative parasympathetic tone [5]. The ANI is obtained using the ANI monitor^®^ (MDoloris Medical Systems, Lille, France). This non-invasive device records the ECG tracing from electrodes placed on the patient’s chest and displays an instant (ANIi) and a 2-min moving mean (ANIm) of the ANI. The Calculation of the ANI was previously described in detail [3, 6, 7]. Briefly, the ANI is an index ranging from 0 to 100 derived from the high-frequency component of heart rate variability modulated by the effect of respiration on the RR series representing relative parasympathetic tone, which reflects the nociception/antinociception balance [7, 8]. High ANI values (above 50) indicate predominant parasympathetic tone, as observed in cases of adequate analgesia [8, 9]. In case of nociception, the sympathetic tone increases and the parasympathetic tone decreases, leading to reduced ANI values (below 50) and hemodynamic reactivity [8, 9].

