### Objective {7}

Following this study, we hypothesized that immediate postoperative pain in PACU could be reduced in patients with low ANI after extubation using a morphine bolus. Consequently, we designed this controlled, randomized study to establish whether the prophylactic administration of morphine at the end of the procedure in patients at risk of postoperative pain (ANI < 50 immediately before extubation) could reduce the incidence of the latter by 50%. Our secondary objective was to determine whether the intraoperative use of goal-directed analgesia with an ANI target of 50 to 80 could improve intraoperative hemodynamics and postoperative outcome.

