### Trial design {8}

The GOALDAN study is an international, multicenter, simple-blind, parallel, prospective, randomized, controlled, two-armed superiority trial. Patients are randomly assigned in a 1:1 ratio in the control group or in the experimental group.

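### The objective is a relative fall in pain incidence, but the only between-arm estimate with a confidence interval named for the primary endpoint is an odds ratio from an optional model

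*Protocol article*

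**What the plan says.** The Objective section asks whether the intervention "could reduce the incidence of the latter by 50" per cent. The Abstract words the primary objective the same way.

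The Statistical methods section for primary and secondary outcomes gives the reason for the primary test as "Since a 50% reduction in the incidence of immediate postoperative pain in PACU patients receiving ANI-directed intraoperative analgesia ranging from 50 to 80 must be" shown. It then specifies a chi-square test, or Fisher's exact test where applicable, on the percentage of patients with NRS > 3. (The article calls the chi-square test paired; that is a separate matter.) No interval is attached to this comparison.

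The same section says the analysis can be completed by a mixed logistic model that allows for site, with covariates chosen on clinical relevance and on univariate results. Type of surgery is among the candidates. For that model, "The results will be expressed in terms of related odds ratios and 95% confidence intervals". It also plans counts and percentages for qualitative variables.

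Two other sections bear on the meaning of the 50%. Trial design describes a "randomized, controlled, two-armed superiority trial". Sample size uses the figure as the effect the trial has the power "to detect a 50% reduction in the incidence of immediate postoperative pain", from a starting point where "immediate postoperative pain can affect 30% of patients". Sequence generation states that randomisation is stratified by centre and by type of surgery.

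**The concern.** The trial's question is on the scale of incidence: by what fraction does the proportion of patients in pain fall? The plan gives a p-value against equality and, optionally, an odds ratio. Neither is an estimate of that fraction with its uncertainty. For the quantitative secondary endpoints, by contrast, the article plans an effect size with a 95% confidence interval.

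The outcome is common, at an assumed 30%, so the odds ratio lies further from 1 than the risk ratio. The odds ratio from the mixed model is also conditional on site and on whatever covariates are selected, so it cannot be turned exactly into a reduction in overall incidence. An odds ratio near 0.5, set beside an objective worded as a 50% fall, is easy to mistake for that fall.

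The primary comparison also leaves out the two factors by which patients are randomised. They enter, at most, through the optional model. The qualitative secondary endpoints follow the same approach as the primary endpoint, so the gap carries over to them.

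**Working it through.** **Inputs.** Control incidence 30%, a 50% relative reduction (so 15%), two-sided 5%, 90% power, 161 per group, and 190 per group to be enrolled (Sample size). Allocation 1:1 (Trial design). As a range for the control rate, 20% to 40% (Background and rationale: "Severe postoperative pain remains a major problem that is seen in 20 to 40% of patients"). That sentence concerns severe pain, so I use it only for sensitivity.

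**1. The article's own figure.** For a test of equal proportions with pooled variance and no continuity correction, where p̄ = (0.30 + 0.15)/2 = 0.225:

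n = [1.960·√(2·0.225·0.775) + 1.2816·√(0.30·0.70 + 0.15·0.85)]² / 0.15²
= [1.960·0.5906 + 1.2816·0.5809]² / 0.0225 = 160.8, rounded up to **161**.

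This matches exactly. Sample size and test therefore agree with each other. Both treat 50% as the alternative in a test of no difference. Power for a true halving is 90.0% at 161 per group and 94.1% at 190.

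**2. Odds ratio against incidence reduction at 30% control incidence.**

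- Halving: OR = (0.15/0.85)/(0.30/0.70) = 0.1765/0.4286 = **0.41**.
- OR of 0.50: odds = 0.50·0.4286 = 0.2143, so incidence = 0.2143/1.2143 = **17.6%**. Relative reduction = 1 − 0.176/0.30 = **41%**.

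**3. Sensitivity to the control rate.**

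| Control incidence | OR for a true halving | Relative reduction when OR = 0.50 |
|---|---|---|
| 20% | 0.44 | 44.4% |
| 30% | 0.41 | 41.2% |
| 40% | 0.375 | 37.5% |

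**4. What a risk ratio with an interval would add.** Three possible results, using the unadjusted log risk ratio with SE = √(1/a − 1/n + 1/c − 1/n), where a and c are the events in the ANI and control arms and n is the number per arm:

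| n per arm | Control events | ANI events | p (chi-square) | Risk ratio (95% CI) | Relative reduction | OR |
|---|---|---|---|---|---|---|
| 161 | 48 | 32 | 0.039 | 0.67 (0.45 to 0.98) | 33% | 0.58 |
| 190 | 57 | 40 | 0.045 | 0.70 (0.49 to 0.997) | 30% | 0.62 |
| 161 | 48 | 24 | below 0.05 | 0.50 (0.32 to 0.78) | 50% | 0.41 |

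The first two rows are the smallest effects that reach p < 0.05 by the uncorrected chi-square test with those control counts. The intervals show how far the data fix the size of the reduction. Even an observed halving is compatible with a reduction of 22% (1 − 0.78). Neither the p-value nor the odds ratio gives a reader that directly.

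**The case against.** The strongest reply is that this is an ordinary superiority design. The article says so, the 50% is the effect it is sized to detect, and the sample size reproduces on that reading. This stands: the test is valid and consistent with the power calculation.

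A reader might infer from the wording of the objective that a significant result would be declared proof of a halving, and that the test is therefore the wrong one. The documents do not support this. No section sets such a rule, a margin or a shifted null. The figures that might be offered in support are also not specific to this trial. Any trial with 90% power at two-sided 5% reaches significance at roughly 1.96/(1.96 + 1.28) = 60% of its design effect or a little more. If the true reduction is exactly 50%, the observed reduction reaches 50% in only about half of trials (52% by exact binomial enumeration at 161 per arm). That is sampling variation around the truth.

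It is also fair to say that percentages per arm will be reported. A reader can divide one by the other and compute a crude interval from the counts. So it would be wrong to say that the plan leaves the incidence reduction unmeasured; what is lacking is a stated estimate with an interval on that scale.

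Finally, the effect measure is often left to the analysis plan, which is not shown, and silence on the risk ratio would not by itself be a finding. Here, however, the article does name an effect measure with an interval, and the one it names is not on the scale of its objective. That part of the point remains.

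**Conclusion.** The point holds as a mismatch between objective and estimate. It is not a fault in the test, the alpha or the sample size. The objective concerns a relative reduction in incidence. The only between-arm contrast with a confidence interval named for the primary endpoint is an odds ratio from an optional model, and the primary comparison has no stated interval and ignores the randomisation strata.

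At 30% control incidence an odds ratio of 0.50 corresponds to a 41% reduction, about 9 percentage points short of a halving. Across control rates of 20% to 40% the corresponding reduction is 44% to 37.5%. These conversions treat the odds ratio as unadjusted. The conditional odds ratio from the mixed model would differ somewhat, in a way the article gives no figures to calculate. That a reader would mistake the odds ratio for the incidence reduction is a reasonable worry, not something the article states.

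The change is worth making because it answers the trial's own question on its own scale at almost no cost.

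**What to change.** In the Statistical methods section for primary and secondary outcomes, name the risk ratio and the risk difference, each with a 95% confidence interval, as the primary effect estimates. Adjust both for the stratification factors, centre and type of surgery, for example by Mantel-Haenszel weighting or by marginal standardisation from the logistic model. Keep the odds ratio as a supplement. Use the same measures for the qualitative secondary endpoints, which follow the primary approach.

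In that section and in Objective, describe 50% as the effect assumed for sizing and success as superiority on the stated test, with the size of the reduction judged from the risk ratio and its interval.

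The cost is revised wording and a few lines of analysis code, with no new data and no extra patients. The stated objective becomes slightly less strong: superiority, with the reduction estimated, in place of a 50% fall.

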### Outcomes {12}

The primary outcome is the immediate postoperative pain in PACU defined by an NRS > 3 during PACU stay. The secondary outcomes are as follows:
Maximum pain score on the first day after surgery (0 to 10 rating scale). The NRS will be assessed every 6 h for the first 24 h (T0 = time of arrival in the PACU).Overall pain management satisfaction score on day 1 after surgery (0–10 NRS).Morphine dose level in PACU (mg).Postoperative nausea and vomiting in PACU.Total dose of morphine administered on the first day after surgery (mg).Duration of PACU stay (time taken to obtain an Aldrete score ≥ 9) (min) [22].Patient destination after surgery (surgical unit, follow-up care, ICU).Incidence of postoperative complications on the first and seventh day after surgery for hospitalized patients using the *Post-Operative Morbidity Survey* (POMS) (Annex 1) [23].Duration of hospital stay (days).Mortality at 28 days.

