### Assignment of interventions: allocation

#### Sequence generation {16a}

Randomization will be performed over the REDCap^®^ website (https://redcap.chu-clermontferrand.fr) to allow immediate allocation. The randomization list is balanced by blocks of variable and undisclosed size and stratified per center and per type of surgery. Patients will be randomized at day 0, after written informed consent is obtained and just before surgery. Each patient will be given a unique patient number and a unique randomization number. It is not possible to change group after randomization.

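### The primary endpoint is assigned a paired chi-square test although the arms are independent, and the test leaves out the randomisation strata

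*Protocol article*

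**What the plan says.** All places are in the protocol article.

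- Primary test, Statistical methods {20a}: the proportions with NRS > 3 "will be compared using the *x*^2^ paired test or Fisher’s exact test".
- Qualitative secondary endpoints, same section: these follow "the same approach as that previously recommended for the primary endpoint".
- Design, Trial design {8}: a "simple-blind, parallel, prospective, randomized, controlled, two-armed superiority trial", in which "Patients are randomly assigned in a 1:1 ratio in the control group or in the experimental group".
- Endpoint, Outcomes {12}: "The primary outcome is the immediate postoperative pain in PACU defined by an NRS > 3 during PACU stay". This gives one yes/no value per patient.
- Randomisation, Sequence generation {16a}: the list is "balanced by blocks of variable and undisclosed size and stratified per center and per type of surgery".
- Adjusted analysis, {20a}: after the primary test, a logistic mixed model that allows for site variability may be added. Type of surgery is among its candidate covariates, and selection also draws on earlier univariate results. The section further provides for comparisons adjusted for factors that might be unbalanced despite randomisation.

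**The concern.** A paired chi-square (McNemar-type) test compares two measurements on the same or matched units and uses only the discordant pairs. This trial has no pairs: different patients sit in each arm, and no section describes matching. As written, the primary test could be computed only by joining each ANI patient to some control patient arbitrarily, and only if the analysed arms happened to be equal in size. The p-value would then depend on how the rows were ordered.

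The second part concerns efficiency. Randomisation is "stratified per center and per type of surgery", but the primary test uses neither factor. If the strata predict pain, stratified allocation reduces the true variance of the difference between arms, and an unstratified test does not take that into account.

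**Working it through.** **1. Which comparison does the sample size assume?** Inputs from Sample size {14}: control rate 30%, halved to 15%, two-sided 5%, 90% power. For two independent proportions with pooled variance under the null, the mean rate is 0.225 and

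n = [1.960·√(2·0.225·0.775) + 1.282·√(0.30·0.70 + 0.15·0.85)]² / 0.15² = [1.960·0.5906 + 1.282·0.5809]² / 0.0225 = 160.8, so 161 per group.

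This is the stated figure. For arbitrarily paired independent patients, the discordant proportion would be 0.30·0.85 + 0.70·0.15 = 0.36 and the McNemar formula gives 163.9, so 164 pairs. The sample size therefore rests on independent arms.

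**2. What would a paired test do to the same data?** The event counts are illustrative. With a and b events in the two arms and k pairs in which both patients have the event, the discordant pairs number a + b − 2k and the statistic is (a − b)² / (a + b − 2k). The numerator is fixed by the data, but k depends only on the pairing.

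*Borderline result, 48/161 against 32/161.* Pearson chi-square is 4.26, p = 0.039. The paired statistic is 256 / (80 − 2k):

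| k | Discordant pairs | p |
|---|---|---|
| 2 | 76 | 0.066 |
| 6 | 68 | 0.052 |
| 7 | 66 | 0.049 |
| 10 (expected k is 48·32/161 = 9.5) | 60 | 0.039 |
| 18 | 44 | 0.016 |

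Significance at 5% requires k ≥ 7. Under random pairing k is hypergeometric, and that happens in about 91% of pairings. Random pairings ranged over about 0.016 to 0.066. The most extreme values seen in two simulations, 5,000 and 20,000 pairings, were 0.014 and 0.070.

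*Result at the planned effect, 48/161 against 24/161.* Pearson p = 0.0013. The paired statistic is 576 / (72 − 2k). Its least favourable value, at k = 0, is 8.0, which gives p = 0.0047. No pairing crosses 5%.

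**3. What does leaving out the strata cost?** The article gives no pain rates by stratum, so the rates here are assumptions. With equal-sized strata and an average rate of 30%, the true variance under the null is smaller than the unstratified test assumes by the ratio

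R = mean of p(1 − p) over strata / (0.30·0.70),

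and the true type I error is about 2·[1 − Φ(1.96/√R)].

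- 25/30/35%: R = 0.2083/0.21 = 0.992, type I error 4.9%.
- 15/30/45%: R = 0.1950/0.21 = 0.929, type I error 4.2%.
- 10/30/50%: R = 0.1833/0.21 = 0.873, type I error 3.6%.

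Simulation at 161 per group with three strata, a common odds ratio and an average ANI-arm rate of 15% agrees:

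| Assumed control rates | Type I error, unstratified / CMH | Power, unstratified / CMH |
|---|---|---|
| 25/30/35% | 5.0% / 5.0% | 90.2% / 90.4% |
| 15/30/45% | 4.3% / 5.0% | 90.7% / 91.7% |
| 10/30/50% | 3.6% / 4.9% | 91.1% / 92.7% |

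A deliberately extreme case, six strata from 5% to 60%, gave a loss of about 2.5 points (92.3% against 94.7%). In every case the unstratified test still has at least 90% power at 161 per group. At the planned 190 per group, the independent-proportions formula gives 94.1%.

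**The case against.** The strongest reply is that the intended test is plain from the rest of the article. Fisher's exact test, offered as the alternative, is for independent groups. So are Student's t and Mann-Whitney, named for the quantitative endpoints, and so is the sample size formula. A statistician would run a Pearson test, and the row-order problem would never arise. That stands as a reading of intent, and it is why a wording slip is the likely explanation. It does not make the sentence correct: it names the primary test, and the qualitative secondary endpoints refer back to it.

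It is also fair that the 48-against-32 example was chosen near the threshold. A reader might infer that the trial's conclusion generally hangs on the pairing. It does not: at the planned effect every possible pairing stays below 0.005.

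On the strata, a reader might infer that the unstratified test inflates the false-positive rate. The calculation shows the reverse. Nor do the documents establish that type of surgery is strongly prognostic. Using it as a stratum and candidate covariate suggests the authors expect it to matter, but with weak strata the gain nearly vanishes.

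Finally, the strata are not absent from the whole plan: the mixed model can carry both site and type of surgery. But that model is optional and secondary, and its covariates are chosen partly from univariate results. The provision to adjust for unbalanced factors does not close the gap either, since blocked stratification is meant to keep these two factors balanced.

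**Conclusion.** The paired chi-square is wrong as written and must be corrected. It contradicts the parallel design, the unpaired alternative in the same sentence and the article's own sample size calculation. If it were taken literally, a borderline primary result could fall on either side of 5% (about 0.016 to 0.066 in the example), while a result at the planned effect would not be in doubt.

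Leaving out the strata is a lesser matter and would be a recommended improvement on its own. The unstratified unpaired test is valid but conservative, with a power loss of roughly 0 to 1.5 points. That size rests on assumed stratum rates, equal strata and a common odds ratio. Neither part calls the sample size into question.

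**What to change.** In Statistical methods {20a}, delete the word that makes the test paired and state:

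- The proportions with NRS > 3 in the two independent arms are compared with a Cochran-Mantel-Haenszel test stratified by centre and type of surgery, or with a logistic regression containing both factors. Name one of the two.
- One effect measure, named in advance, is reported with its 95% confidence interval.
- A rule for pooling sparse strata is fixed before unblinded data are seen, and no covariate in the primary analysis is chosen from univariate results.
- The unpaired Pearson chi-square, or Fisher's exact test where counts are sparse, is supportive.
- The same approach applies to the qualitative secondary endpoints.

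The cost is a short change to the statistical section and agreement on the pooling rule, settled before the interim analysis if that is still ahead. No additional patients or data are needed, and 161 per group (190 enrolled) stays as it is.
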